#### Post-hoc analysis of the power of the study :

The recruitment was lower than expected over the planned duration of the study and the power remained above 80% with an effective standard deviation in reduction in pain by 2.1 in post-hoc analysis.

#### 12 – Framework

The adopted test framework is based on non-inferiority hypothesis.

#### 13a – Statistical interim analyses and stopping guidance - Information

No statistical interim was performed.

#### 13b – Statistical interim analyses and stopping guidance – planned adjustment

Not applicable.

#### 13c – Statistical interim analyses and stopping guidance – Details of guidelines

Not applicable.

#### 14 – Timing of outcome analysis

The statistical plan analysis (SAP) for the final analysis of the trial was developed prior to database lock. The SAP will be reviewed and approved by an independent methodological comity and the principal investigator.

#### 15 – Timing of outcome assessments

The parameters and scale were evaluated at different visits in accordance with the following table.

|                                                   | Inclusion
Randomisation
T0    | T10                                 | T20                                 | T30                                 | T40                                 | T50                                 |                                     |
|---------------------------------------------------|-------------------------------------|-------------------------------------|-------------------------------------|-------------------------------------|-------------------------------------|-------------------------------------|-------------------------------------|
| - Inclusion / exclusion criteria check            |  |                                     |                                     |                                     |                                     |                                     |                                     |
| - Patient consent                                 |  |                                     |                                     |                                     |                                     |                                     |                                     |
| - Demographic parameters.                         |  |                                     |                                     |                                     |                                     |                                     |                                     |
| - numerical scale of self-evaluation of pain (EN) |  |  |  |  |  |  |                                     |
| - Non-invasive blood pressure                     |  |  |  |  |  |  |                                     |
| - Heart rate and respiratory rate                 |  |  |  |  |  |  |                                     |
| - Sedation score                                  |  |  |  |  |  |  |                                     |
| - Oxygen saturation and flow                      |  |  |  |  |                                     |                                     |                                     |
| - The sedation scale                              |  |  |  |  |                                     |                                     |                                     |
| - Injected and sprayed volumes                    |  |  |  |                                     |                                     |                                     |                                     |
| - Co-analgesia                                    |                                     |                                     |                                     |                                     |                                     |                                     |  |
| - Adverse Events                                  |                                     |                                     |                                     |                                     |                                     |                                     |  |

## **4. Statistical Principles**

#### 16 – Confidence intervals and P values - Level of statistical significance

The threshold  $p \leq 0.025$  will be taken into account to define the significance of the statistical tests.

#### 17 – Confidence intervals and P values - Description

No adjustment for multiplicity will be taken into account.

#### 18 – Confidence intervals and P values – Confidence intervals to be reported

The exact method will be taken into account to calculate the confidence interval.

#### 19a – Adherence and protocol deviations – Definition of adherence

Adherence to the protocol will be defined as compliance with the criteria for inclusions and exclusions of the protocol and adherence to treatment.

Premature discontinuation of study treatment will be considered as a non-adherence to the protocol.

#### 19b – Adherence and protocol deviations – Description of adherence

Adherence to the protocol will be listed in the CONSORT flow diagram.

#### 19d – Adherence and protocol deviations – Description of protocol deviations to be summarized

Premature discontinuation of study treatment will be recorded as a protocol deviation and listed in the CONSORT flow diagram.

#### 20 – Analysis populations

The PP population will consist of all randomized patients without any major deviation from the protocol. The following deviations from protocol will lead to exclusion from the PP population:

- Subject withdrawing consent to participate in the study.
- Non-adherence to the protocol (Overdosing, underdosing, discontinued intervention).
- No respect of inclusion criteria.

The ITT population will consist of all patients who have been randomized. Patients will be analyzed in the study arm assigned.

## **5. Trial Population**

#### 21 – Screening data

Numbers of patients assessed for eligibility with acute traumatic pain will be presented in the CONSORT flow Diagram.

#### 22 – Eligibility

All adults presenting to the emergency department with pain due to recent trauma and self-rated intensity  $\geq 6$  on the numeric pain scale.

This pain can be either permanent or triggered or aggravated paroxysmally by movements or mobilizations.

Proposed subjects for the study will meet each of the following criteria:

- Age between 18 and 75 years.
- Person affiliated with social security or beneficiary of such a scheme.
- Informed and written consent signed by the patient or their legal representative.

Subjects that meet at least one of the following criteria cannot be included:

- Age under 18 years or upper 75 years.
- Severe traumatized patient of grade A or B (cf Annex 6 classification TREUNAU).
- Pain of medical origin (eg chest pain, abdominal pain, headache ...).
- History of chronic respiratory, renal or hepatic insufficiency.
- Substance addiction.
- Pregnant woman / breastfeeding.
- History of medico-surgical sinus.
- SpO2 <90%.
- Systolic blood pressure <90 mmHg.
- Opioid Allergy.
- Patient with head trauma and neurological involvement (GCS score <14).
- Patient with facial massive trauma.
- Patient unable to understand or score pain EN.
- Patient who received an analgesic-type analgesic (level 3) within 6 hours before taking charge.
- ALR indication.
- Obstruction of nasal passages treated with nasal decongestants (particularly oxymetazoline) within 20 minutes of admission.
- Protected persons referred to in Articles L1121-5 to L1121-8 of the CSP.
- Uncontrolled epilepsy.
- Intracranial hypertension.
- Weight upper 100kg.

### 23 – Recruitment

Numbers of patients and reasons for withdrawal and/or exclusion from analysis will be presented in the CONSORT flow diagram.

### 24a – Withdrawal / follow-up - Level

Timing of withdrawals and patients lost to follow up will be presented.

24b – Withdrawal / follow-up – Timing / Lost of follow-up data

Timing of withdrawals and patients lost to follow up will be presented in CONSORT diagram format, with numbers and reasons for withdrawal and/or exclusion from analysis.

24c – Withdrawal / follow-up – Reasons and details

The reasons and details of the withdrawal / follow-up data presentation will be listed by categories (inadequate concentration in packaging kits, not meeting inclusion criteria, overdosing, underdosing, discontinued intervention).

25a – Baseline patient characteristics – List of baseline patient characteristics to be summarized

Patients will be describe at inclusion by age, gender, weight, trauma area (Head, shoulder, Arm/ elbow, Wrist / hand, Thorax wall, Rachis, Pelvis / hip, Leg / knee, Ankle or foot) vital parameters (Heart Rate, Respiratory Rate, Mean Arterial Pressure, numerical Rating Scale for pain), Co-analgesia ( paracetamol, Codeine, Ketoprofen).

25b – Baseline patient characteristics – Details

Baseline and demographic characteristics will be summarized for PP population. Descriptive summary statistics will be used for reporting continuous (arithmetic median and Inter Quartile Rate) and categorical (numbers and percentages) variables.

## 6. Analysis

### 26a – Outcome definitions – specifications and timing

See section 15 « Timing of outcome assessments”.

### 26b – Outcome definitions – measurement and units

Not applicable

### 26c – Outcome definitions – transformation used

Not envisaged.

### 27a – Analysis methods - presentation

- Principal objective analysis :

The main objective is to compare the efficacy of analgesia after 30 min performed by intranasal Sufentanil compared to the reference treatment (Intravenous Morphine).

Outcome: The analysis criterion corresponds to the variation of the numerical scale of the pain (EN at T30 – EN at T0) between the reference treatment (Morphine IV) and the tested treatment (Sufentanil IN).

Population of analysis: The analysis of the main objective will focus on the per-protocol (PP) population, that is to say on all patients included hospitalized in emergencies without major violation to the protocol integrating in particular patients who received the treatment dose provided for in protocol.

Analysis: The non-inferiority of the study treatment compared to the reference treatment in terms of variation of the numerical scale of pain (EN at T30 – EN at T0) will be evaluated using a one sided mean-equivalence t test on the per protocol population. We used the TOSTT procedure (*Dinno A. 2015. tostt: mean-equivalence t tests, Stata software package*) that tests the equivalence of means in a symmetric equivalence interval using the two-tailed unilateral test approach (Schuirmann 1987).

The equivalence threshold corresponds to the minimal, clinically significant, change in the level of pain; It has been defined a priori as a modification of 1.3 of the numerical scale (EN).

The statistical threshold of significance will be  $p < 0.025$ .

- Secondary objectives analysis :

- The objective n°2 is to compare the efficacy of analgesia performed by intranasal Sufentanil compared to the reference treatment (IV Morphine) after 10 min and 20 min of treatment.

Outcome: The analysis criterion corresponds to the variation of the numerical scale of the pain (EN at T10 or T20 – EN at T0) of each treatment (Sufentanil IN versus Morphine IV).

Population of analysis: The analysis will be carried out on the per-protocol (PP) population and then on the intention-to-treat (ITT) population of patients hospitalized in the emergency department.

Analysis: The evaluation of the efficacy of analgesia of pain at intermediate times will be carried out between treatment groups.

The comparative analysis of the variation of the numerical scale of the pain (EN at T10 or T20 – EN at T0) will be carried out using the two group Student t test (a two-sided test). The statistical threshold of significance will be  $p < 0.05$ .

- The objective n°3 is to evaluate the efficacy of analgesia performed by intranasal Sufentanil and Morphine IV, after 10 min and 20 min of treatment.

Outcome: The analysis criterion corresponds to the measurement of the numerical scale (EN) of pain at the initial and final times (EN evaluated at 10 and 20 min) in each of the treatment groups (Sufentanil IN versus Morphine IV).

Population of analysis: The analysis will be carried out on the per-protocol (PP) population and then on the intention-to-treat (ITT) population of patients hospitalized in the emergency department.

Analysis: The evaluation of the effectiveness of analgesia of pain at each intermediate time will be performed according to the treatment group.

The comparative analysis of the measurement of the numerical scale of the pain (10 or 20 min) will be carried out using the Student's test for paired series in each group (a two-sided test). The statistical threshold of significance will be  $p < 0.05$ .

- The objective n°4 is to compare the occurrence of adverse effects between treatment groups (Sufentanil IN versus Morphine IV).

Outcome: The analysis criterion corresponds to the evaluation of the following adverse effects in each of the treatment groups: Nausea, vomiting, epistaxis, discomfort in the nasal

passages, deep sedation (sedation scale > 2), desaturation <90%, pressure arterial <90 mmHg, respiratory rate <10 / min, use of Naloxone (antidote).

Population of analysis: The analysis will be carried out on the per-protocol (PP) population and then on the intention-to-treat (ITT) population of patients hospitalized in the emergency department.

Analysis: The comparative analysis of adverse effects between treatment groups (Sufentanil IN versus Morphine IV) will be performed using the chi-2 test and by an exact Fisher test when the expected value of a contingency table cell will be less than 5.

The statistical threshold of significance will be  $p < 0.05$ .

- The objective n°5 is to evaluate the feasibility in pre-hospitalized patients.

The objective is to evaluate efficacy of analgesia performed by intranasal Sufentanil compared to the reference treatment (IV Morphine) after 10 min, 20 min and 30 min of treatment in the group of pre-hospital patients. The objective is to evaluate patient satisfaction.

Outcome: The analysis criterion corresponds to the variation of the numerical scale of the pain (EN at 10 min, 20 min and 30 min – EN at T0) of each treatment (Sufentanil IN versus Morphine IV).

Population of analysis: The analysis will be performed on the pre-hospital patient group of 30 subjects.

Planned analysis: A descriptive evaluation of the effectiveness of analgesia of pain at each time and the satisfaction of the patient with regard to its management will be carried out between treatment groups. The comparative analysis of the variation of the numerical scale of the pain (EN at 10 min, 20 min and 30 min – EN at T0) will be carried out using a repeated measures analysis of variance integrating if necessary the correction from Greenhouse-Geisser;

The recruitment of patients in the pre-hospital group is not sufficient to achieve this goal.

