##### **Version 2.0 of April 29, 2014 [name] (Protocol version 8.0 – 29/04/2014):**

This study will involve a sample size of 198 patients (99 patients per group). In order to guarantee this number of analyzable patients, we envisage a complementary recruitment of 10 patients per group. The calculation of the number of patients required corresponds to a non-inferiority study design.

The null hypothesis corresponds to a difference in efficacy between treatment groups above the equivalence threshold; The alternative hypothesis allows us to conclude that the treatments are equivalent;

The primary endpoint is the difference, before / after, of the mean pain score assessed by a numerical scale at inclusion and 30 minutes after administration.

The number of subjects required was assessed by the Schuirmann method, taking into account a minimal, clinically significant value of pain level evolution defined a priori as a modification of 1.3 of the numerical scale (EN), an alpha risk of 2.5% and a standard deviation of the response of 2.8.

A total of 99 subjects per group will thus be necessary to reject the null hypothesis of a difference in efficacy and to conclude that the evaluated treatment is not inferior compared to the reference treatment, in terms of the evolution of EN in the first 30 minutes, with a power of 80%.

This calculation was performed using the NQuery Advisor software version 7.0 (Statistical Solutions Ltd., Boston MA, USA).

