#### 29 – Additional analyses

- Principal outcome analyzes (sensitivity analysis) :

Sensitivity analysis of the primary objective: The evaluation of the non-inferiority of intra-nasal Sufentanil compared to the reference treatment conducted on the per-protocol population (PP) will be confirmed on the intention-to-treat population (ITT) in sensitivity analysis to comply recommendations of the guidelines (JAMA, 2012). This will be evaluated using a Schuirmann test on the imputed data. This analysis will retain the 2.5% as the statistical threshold.

In practice for a more robust result, both analyzes (PP and ITT) must be performed and give similar results.

- Principal outcome analyzes (complementary analysis) :

The evaluation of the superiority of intra-nasal Sufentanil compared to the reference treatment is used in hierarchical analysis. This will be evaluated on the intention to treat analysis using a two sample Student t test after verification of the application conditions.

Although unilateral testing appears to be most consistent with therapeutic hypotheses, we used a two-sided test. By decreasing the risk of alpha error on the conclusion of superiority, a two-sided test is more conservative.

This analysis will retain the 5% as a statistical threshold. This analysis will not require adjustment of the statistical threshold.

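### The non-inferiority claim is assigned a symmetric ±1.3 equivalence test, which as written penalises a better sufentanil arm and severely narrows the route to the planned superiority test

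*SAP*

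**What the plan says.** Section 12 is explicit about the framework: "The adopted test framework is based on non-inferiority hypothesis". The version 3.0 entry in section 4a, and section 4b, make superiority conditional on demonstrated non-inferiority. Section 29 agrees: "The evaluation of the superiority of intra-nasal Sufentanil compared to the reference treatment is used in hierarchical analysis", as a two-sided 5% t test on ITT.

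The test itself is described differently. Section 27a says non-inferiority "will be evaluated using a one sided mean-equivalence t test on the per protocol population", at a 2.5% threshold. It then names the Stata tostt procedure, which "tests the equivalence of means in a symmetric equivalence interval using the two-tailed unilateral test approach", with a threshold of 1.3 points on the pain scale. Section 29 confirms the result on ITT with a Schuirmann test on imputed data, also at 2.5%.

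Section 11 (version 2.0) sizes the trial by the Schuirmann method and states: "The alternative hypothesis allows us to conclude that the treatments are equivalent".

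**The concern.** A non-inferiority test asks one question: can we exclude that sufentanil is worse by 1.3 points or more? Two one-sided tests in a symmetric interval ask a second one as well: can we exclude that it is better by 1.3 points or more? Only if both are answered yes does the procedure succeed. A large benefit therefore makes success less likely.

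Two things are at stake. First, the same data could give opposite primary conclusions, depending on whether the analyst uses both bounds or only the inferiority bound, and the SAP does not say which. Second, superiority is gated on the primary result. If the gate needs both bounds, it tends to close when sufentanil really is better.

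**Working it through.** **Inputs.** From section 11, version 2.0: margin 1.3, "an alpha risk of 2.5% and a standard deviation of the response of 2.8", power 80%, 99 per group. From section 11, version 1.0: SD 2.2, 99 per group, power 97%. From the post-hoc paragraph of section 11: SD 2.1, with recruitment below plan and no achieved N. Benefit means a larger fall in pain on sufentanil, so sufentanil minus morphine in (EN T30 − EN T0) is negative.

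**Step 1: which test gives 99 per group?**
- Two-bound test at true difference 0, normal approximation (the type II error splits over two bounds): n = 2 × [2.8 × (1.960 + 1.282) / 1.3]² = 97.5, so 98. The exact t-based calculation gives power 79.7% at 98 and 80.3% at 99, hence 99. The plan's figure is reproduced.
- One-sided non-inferiority: n = 2 × [2.8 × (1.960 + 0.842) / 1.3]² = 72.8, so 73 (74 by exact t). Its power at 99 is 90.2%.
- Version 1.0 check (SD 2.2, 99 per group): two-bound 97.1%, one-sided 98.5%, stated 97%. This also favours the two-bound test but is not decisive alone.

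The version 2.0 sample size is therefore an equivalence figure.

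**Step 2: what must be observed to pass (99 per arm, SD 2.8)?**
- SE = 2.8 × √(2/99) = 0.398. With t(0.975; 196 df) = 1.972, the 95% CI half-width is 0.785.
- The two-bound test passes only if the observed absolute difference is below 1.3 − 0.785 = 0.515.
- Two-sided 5% superiority on the same patients needs a benefit above 0.785.

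On a single data set with this SE the two regions do not overlap. At SD 2.1 the SE is 0.298 and the limits are 0.711 and 0.589, so a narrow window exists. On the same data that window closes below 82 per arm.

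**Step 3: probability of passing the primary test (99 per arm, SD 2.8, exact).**

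| True benefit | Two bounds | One-sided non-inferiority |
|---|---|---|
| 0 | 80.3% | 90.2% |
| 0.5 | 51.1% | 99.4% |
| 1.0 | 11.3% | 99.99% |
| 1.3 | 2.5% | about 100% |

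At benefit 1.3 the 2.5% is simply the size of the test at its upper-benefit boundary.

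**Step 4: passing the gate and then superiority, with the populations the SAP uses.** The gate is on PP and superiority is on ITT. I simulated 99 PP patients nested in 110 ITT patients per arm, assuming complete data and the same effect and SD in both sets. The 110 is the target in section 4b.
- SD 2.8: joint success is below 0.5% at every benefit from 0.5 to 1.3. For scale, ITT superiority power at benefit 1.0 is about Φ(1.0 / [2.8 × √(2/110)] − 1.971) = Φ(2.649 − 1.971) = Φ(0.678), or 75%.
- SD 2.1: joint success is about 19% at benefit 0.5 and 0.8, 11% at 1.0 and 2% at 1.3. With a one-sided gate the figures are 42%, 80%, 94% and over 99%.

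**The case against.** The best defence is that section 27a speaks of non-inferiority, calls the test one-sided and gives one p-value threshold. tostt is built from two one-sided tests, and an analyst could report only the inferiority bound. The SAP never states that both must reject. That stands as far as it goes: the document conflicts with itself, and it does not prove that both bounds will be applied. It does not remove the point, because no section selects the inferiority bound, while the named procedure, the ITT confirmation, the section 11 hypotheses and the sample size all follow the two-bound test.

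A reader might infer that superiority can never be reached if sufentanil is better. The documents do not support this. Gate and superiority test use different populations, a modest benefit can pass both bounds, and at the SD of 2.1 in section 11 joint success is possible at 99 per arm.

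A reader might also infer that a false non-inferiority claim is made more likely. It is not: passing both bounds implies passing the inferiority bound, so the procedure is conservative for that claim.

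Nor can one say that equivalence is wholly foreign to the plan, since section 11 states it as the alternative. It is, however, not the framework in section 12. Finally, superiority is only a complementary analysis added at the May 2016 blind review, which limits the weight of the second consequence but not of the first.

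**Conclusion.** The point holds as a conflict over the primary decision rule. The declared aim is non-inferiority; the named procedure is symmetric equivalence, and the sample size was computed for it. Applied as written, the rule cuts the chance of a positive primary result from 99% or more to 51%, 11% and 2.5% at true benefits of 0.5, 1.0 and 1.3 (99 per arm, SD 2.8). The route to superiority is severely restricted rather than closed. The harm is a false negative on the primary claim and a gate that works against real benefit.

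The figures assume 99 PP patients per arm, and the joint figures also assume the nested ITT set of 110. The achieved number is not given. At SD 2.1, two-bound power at zero difference stays at or above 80% down to 56 per arm, so 56 to 99 per arm is a plausible assumed range. Smaller numbers would narrow the joint window further.

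**What to change.** 1. In sections 27a and 29, replace the tostt and Schuirmann wording with one one-sided 2.5% test. Non-inferiority is concluded if the upper limit of the two-sided 95% CI for sufentanil minus morphine in (EN T30 − EN T0) is below +1.3, on PP and confirmed on ITT.
2. Keep superiority as the separate two-sided 5% test on ITT. It should not be read from the PP interval, because sections 4b and 29 place it on ITT.
3. In section 11, rewrite the hypotheses as non-inferiority and drop the Schuirmann reference for the decision rule. Restate the power of 99 per group at SD 2.8 as about 90% for the one-sided test, noting that 80% is the two-bound figure. Changing only the hypotheses would leave method and power mismatched to the test.
4. Enter the change, its date and its reason in sections 4a and 4b. Version 3.2 answers a manuscript reviewer, so a change made now follows the data and must be disclosed as such. Reporting the two-bound result beside the one-sided one would keep this transparent.

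The cost is wording, a small change of code and a disclosed late amendment. Enrolment is unaffected. What is given up is the two-sided equivalence conclusion in section 11.
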